**Methods:**

This is a hybrid effectiveness-implementation type-1 trial, determining the effectiveness of the intervention while evaluating the context of its implementation in Madagascar’s Analamanga region, containing the capital, Antananarivo. Using a stratified cluster randomized design, 61 public-sector primary-care health facilities were randomized within 6 strata to either receive the intervention or not (29 intervention vs. 32 control facilities). The strata were defined by a health facility’s antenatal care visit volume and its capacity to offer facility-based deliveries. The registered pre-specified primary outcomes are (i) delivery at a health facility, (ii) antenatal care visits, and (iii) total healthcare expenditure during pregnancy, delivery, and neonatal period. The registered pre-specified secondary outcomes include additional health outcomes, economic outcomes, and measurements of user experience and satisfaction. Our estimated enrolment number is 4600 women, who completed their pregnancy between July 1, 2020, and December 31, 2021. A series of nested mixed-methods studies will elucidate client and provider perceptions on feasibility, acceptability, and usefulness of the intervention to inform future implementation efforts.

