#### Population survey-based impact evaluation

Data collection will be performed after the conclusion of the intervention period on 01/01/2022 (Fig. 2). The population-based survey will be conducted by a team of trained research assistants with experience in qualitative and quantitative research. Research assistants will be trained and supervised by the study team. All questionnaires contain questions in English with Malagasy translations. The survey will be conducted in Malagasy. The primary sampling unit is a census enumeration area (Malagasy: “fokontany”). We will randomly select one census enumeration area from each of the catchment areas of each public-sector primary-care health facility participating in this trial. Within each census enumeration area, we will then select all households and interview all consenting women meeting the eligibility criteria. This sampling scheme is self-weighting [52]. During the interview, the women’s maternal health booklet will be consulted and photographed to reduce recall bias. During the interviews, we will collect data from two sources: (i) the maternal health booklet, which all women utilizing ANC receive, and (ii) women’s self-report. These two data sources will allow us to measure all of our primary outcomes and will contribute to a mechanistic understanding between exposure and outcomes. In particular, we will extract the data on ANC visits from the maternal health booklet and elicit self-reported data on all outcomes, including ANC visits. In addition, the interviews will elicit data on demographic, behavioral, and socioeconomic factors. Total patient expenditure will be calculated from direct costs (medication, diagnostic, operation during pregnancy, delivery and neonatal period, referral costs) and indirect costs (opportunity costs).

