### Randomization and blinding

The randomization scheme of this trial is shown in Fig. 3. The unit of randomization for the intervention was one public-sector primary-care health facility. Health facilities in Antananarivo Atsimondrana, Avaradrano, and Renivohitra health districts in the Analamanga region have catchment areas of between 200 and 30,495 inhabitants (mean 3666) and perform 40 to 5438 ANC visits (mean 1556) per year [54, 55]. Randomization of health facilities was performed before the start of the intervention. All 61 public-sector primary-care health facilities in the study region were stratified into 6 subgroups in two stages. In stage one, strata were defined by a health facility’s ANC visit volume (stratum 1: 0–1750, stratum 2: 1750–3500, and stratum 3: >3500 ANC visits per month, respectively). In stage two, strata were defined by the capacity to perform facility-based deliveries (stratum A: no deliveries, stratum B: >1 delivery). Prior empirical evidence indicates that ANC and facility-based delivery quality differ significantly depending on a facility’s patient volume and capacity to perform deliveries [56]. Thus, the sample was stratified by these characteristics to ensure adequate representation of the different kinds of facilities in the final sample. Within each stratum, the facilities were sorted in descending order of the expected number of ANC visits based on the number of reported ANC visits during the year 2017. A pairwise randomization was then applied by a senior biostatistician. The first two health facilities in each stratum were randomly assigned to either the intervention or control group of the study. The algorithm was then repeated until all health facilities were assigned. In addition, four reference hospitals were intentionally assigned to receive the intervention to ensure that women could use the MMHW in case of referral for complications during pregnancy and/or delivery. Due to the nature of the intervention, neither participants nor health facility staff or primary data collectors can be blinded to allocation. Allocation of the intervention will be concealed from outcome assessors including secondary assessors and data analysts.

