### Analysis

#### Power calculation

For our baseline power calculation, we assumed a facility-based delivery rate of 67% and an average count of two ANC visits during pregnancy without the intervention [35]. The potential study population was approximately 10,000 pregnant women in the study region during the intervention period. We assumed that 50% of participants living in catchment areas of health facilities that received the intervention would adopt the MMHW. We calculated the minimum detectable difference between the intervention and control groups for the three primary outcomes using methods for cluster randomized trials. We assumed a 20% loss to follow-up and an intra-cluster correlation of 0.05. The intra-cluster coefficient (ICC) was conservative compared to ICCs that were empirically measured in similar settings [57]. Using the standard method for power calculations for binary outcomes, with a 95% two-sided confidence level, we would have 80% power to detect a 4-percentage point increase in the rate of facility-based deliveries, an 80% power to detect an increase of 0.08 average ANC visits per woman, and an increase of total health expenditure of 1700 Malagasy Ariary if we enrolled 2300 participants per group.

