#### Analysis of the randomized controlled trial

Our primary analysis will be an intent-to-treat (ITT) causal effect estimation of our registered pre-specified primary and secondary outcomes. The effect sizes determined in the primary analysis provide an unbiased measure of the real-life policy impact of our intervention. As a secondary analysis, we will also conduct a contamination-adjusted intention-to-treat analysis (CA ITT) using an instrumental variable to adjust for bias [58]. For the CA ITT analysis, we will use the random assignment to intervention vs. control facility catchment area of this trial as an instrumental variable (IV) to measure the effect size that would have been attained without “contamination.” Contamination occurs when women who live in an intervention area do not utilize the MMHW and women who live in a control area utilize the MMHW to receive health care. The treatment in the IV analysis is participants’ actual MMHW registration status. The effect size determined in this secondary analysis provides a measure of the full effect that the intervention would have induced in the absence of intervention utilization (or lack thereof) that did not conform with the intervention status intended by the random assignment of geographical communities. We will regress the primary and secondary outcomes (Table 1) on the random assignment of participants to facility catchment intervention vs. control area. For our binary outcomes, we will use modified Poisson regression analysis [59]; for our count outcomes, we will use negative binomial regression; and for our continuous outcomes, we will use linear regression for effect size estimation.

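### The analysis section names woman-level regressions on assignment and states no allowance for the randomised facility or the six strata; run as written, intervals would be about half the correct width at the protocol's own ICC

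*Protocol article*

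**What the plan says.** The Abstract gives the design: "61 public-sector primary-care health facilities were randomized within 6 strata to either receive the intervention or not (29 intervention vs. 32 control facilities"). The section Randomization and blinding confirms it: "The unit of randomization for the intervention was one public-sector primary-care health facility". Within each stratum, facilities were sorted by their 2017 antenatal care (ANC) volume, and "A pairwise randomization was then applied by a senior biostatistician".

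The section Population survey-based impact evaluation says: "We will randomly select one census enumeration area from each of the catchment areas of each public-sector primary-care health facility participating in this trial". Each woman therefore belongs to one sampled area and one randomised facility, and the two levels coincide.

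The section Analysis of the randomized controlled trial then gives the intention-to-treat model: "We will regress the primary and secondary outcomes (Table 1) on the random assignment of participants to facility catchment intervention vs. control area". Binary outcomes get modified Poisson regression, counts get negative binomial, and continuous outcomes get linear regression. The section names no cluster-robust variance, random effect, GEE, cluster-level summary, stratum or pair. It also does not say that women will be treated as independent.

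The strata are defined by ANC volume and delivery capacity. The volume cut-points are printed in monthly units, for example "stratum 3: >3500 ANC visits per month". The same section says that the facilities "perform 40 to 5438 ANC visits (mean 1556) per year".

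**The concern.** Women served by the same facility share staff, pharmacy prices, distance to care and the intervention itself, so their outcomes are correlated. The evidence comes from 61 randomised units, not from 4600 independent women. An analyst who implements the section exactly as printed would get standard errors that treat the women as independent. This is the default for negative binomial and linear regression. It is also what a modified Poisson sandwich variance gives unless a cluster variable is declared.

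The error would run in one direction: intervals too narrow and too many false positives on outcomes meant to guide national policy. Leaving out the strata is a different and lesser matter. It wastes precision that the stratified, volume-ordered allocation was designed to give. To use the strata, the analyst must also be able to identify them, and the printed cut-points do not allow that.

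**Working it through.** **Inputs.**
- Facilities: 61 (29 intervention, 32 control), from the Abstract.
- Sample: the power section states its detectable differences "if we enrolled 2300 participants per group", so 4600 in all.
- ICC 0.05, 20% loss, facility-delivery rate 67%, detectable increase 4 points, 80% power, two-sided 5%: all from Power calculation.
- It is not clear whether 2300 is before or after loss, so I carry both 2300 and 2300 × 0.8 = 1840 per group.

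**The plan's own figure.** Two-proportion power for 67% against 71% (pooled variance):

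| Calculation | n = 2300 per group | n = 1840 per group |
|---|---|---|
| Power for 4 points, no design effect | 83.5% | 74.7% |
| Minimum detectable difference, no design effect | 3.8 points | 4.3 points |
| Power for 4 points, ICC 0.05 | 27% | 26% |
| Minimum detectable difference, ICC 0.05 | 8.1 points | 8.3 points |

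The stated 4 points is reproduced only when the design effect is left out, although the section says cluster methods were used.

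**Design effect.** DE = 1 + (m − 1) × ICC, where m is women per facility.
- m = 4600/61 = 75.4, so DE = 1 + 74.4 × 0.05 = 4.72 and √DE = 2.17.
- m = 3680/61 = 60.3, so DE = 1 + 59.3 × 0.05 = 3.97 and √DE = 1.99.

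**Interval width if clustering is ignored.** Ratio to the correct width = 1/√DE = 0.46 (m = 75.4) or 0.50 (m = 60.3). For 67% against 71% with 2300 per group, SE = √[(0.67 × 0.33 + 0.71 × 0.29)/2300] = 0.0136. The half-width is 1.96 × 0.0136 = 2.7 points when women are treated as independent, and 2.7 × 2.17 = 5.8 points with clustering. With 1840 per group the figures are 3.0 and 5.9 points.

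**False-positive rate.** Under the null, P(|Z| > 1.96/√DE). With DE = 4.72, 1.96/2.17 = 0.90, giving 36.7%. With DE = 3.97, 1.96/1.99 = 0.98, giving 32.5%.

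**Simulation.** Beta-binomial data under the null (rate 67%, ICC 0.05, 29 against 32 facilities, 20,000 runs):

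| Women per facility | Rejection rate, woman-level robust SE | Rejection rate, facility-level SE with t on 59 df | Width ratio |
|---|---|---|---|
| 75 | 36.7% | 5.0% | 0.45 |
| 60 | 32.2% | 4.8% | 0.49 |

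**Dependence on the ICC** (first value m = 75.4, second m = 60.3):

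| ICC | DE | Width ratio | Type I error |
|---|---|---|---|
| 0.01 | 1.74, 1.59 | 0.76, 0.79 | 13.8%, 12.0% |
| 0.02 | 2.49, 2.19 | 0.63, 0.68 | 21.4%, 18.5% |
| 0.05 | 4.72, 3.97 | 0.46, 0.50 | 36.7%, 32.5% |
| 0.10 | 8.44, 6.93 | 0.34, 0.38 | 50.0%, 45.7% |

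**Unequal cluster sizes.** All eligible women in one area are interviewed, so the numbers will vary. The protocol gives no coefficient of variation (CV). Assuming 0.5 to 1.0, with DE = 1 + ((1 + CV²)m − 1) × ICC and ICC 0.05, the ratio falls to 0.34–0.46.

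**Stratum cut-points.** The largest facility has 5438 visits per year, or 5438/12 = 453 per month. Leaving the lowest volume stratum would take more than 1750 per month, or 1750 × 12 = 21,000 per year. As printed, no facility reaches volume stratum 2 or 3. At most two of the six strata (with and without deliveries) would then contain facilities.

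**The case against.** The strongest reply is that the article is silent on variance and has not made a wrong choice. The paragraph names an exposure and mean models for estimating effect sizes; it does not discuss standard errors. All three models accept a facility-clustered sandwich variance without changing the mean model. The article calls the design cluster-randomised, gives an ICC, and promises that the full protocol will be public. A statistical analysis plan may specify the variance.

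Much of this stands. A reader might infer that the plan has decided on an unclustered analysis, but the text never says so. A reader might also take the power figure, which matches only a calculation without a design effect, as proof that the analysis will ignore clustering. It is not proof; it is a separate problem in the power section. It does make an unstated adjustment less safe to assume.

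Three further limits also stand:
- The half-width result comes from clustering alone. Omitting strata or pairs usually makes intervals too wide.
- The size depends on the ICC, and the protocol calls 0.05 conservative.
- Not every entry in Table 1 is a woman-level outcome. The implementer's direct costs and the supplements distributed according to facility records are not.

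A reader might also want negative binomial replaced by Poisson on grounds of under-dispersion. The article gives no variance for ANC visits, so that would be a preference and not a correction.

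What the reply does not remove is that the section names a regressor and a model for each outcome type and, followed literally, gives wrong error bars. The mismatch of monthly and yearly visit volumes is a contradiction within one section, not an omission that another document could fill.

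**Conclusion.** The point holds as an omission with serious consequences if the text is followed literally. At ICC 0.05 and 60 to 75 women per facility, intervals would be 0.46 to 0.50 of the correct width, and a nominal 5% test would reject a true null about 32 to 37% of the time. At ICC 0.01 the ratio is 0.76 to 0.79 and the error rate 12 to 14%, still more than double the nominal level. These figures assume that clustering is ignored altogether and that facilities contribute equal numbers; unequal numbers would make matters worse. They apply to woman-level outcomes. The missing stratum terms cost precision, not validity. The stratum units are a secondary error but must be corrected, because the strata cannot be rebuilt from the text as printed.

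**What to change.** In the analysis section, keep the three mean models and add three statements:
- For all woman-level outcomes, the variance is clustered on the randomised facility, with a small-sample correction suited to 61 clusters.
- The six randomisation strata enter as fixed effects.
- Optionally, the facility's 2017 ANC count, which ordered the pairs, enters as a covariate.

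In Randomization and blinding, reconcile the unit of the volume cut-points with the yearly volumes, checking against the actual randomisation list.

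The cost is small. Facility-level degrees of freedom go from 61 − 2 = 59 to 54 with five stratum indicators, or to 53 with the ANC count. The two-sided 5% t value moves from 2.001 to 2.005 or 2.006. The assignment list and the 2017 counts already exist. The article places outcome assessment from January 2022, so the wording could be settled before any outcome data are seen.

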**Primary outcomes**			
Facility-based delivery^a^	Woman delivering at a health facility	Binary variable	Quantitative household survey
ANC visits^a^	ANC visits at a health facility per woman	Count variable	Quantitative household survey
Total healthcare expenditure^a^	Total health expenditure during pregnancy, delivery and neonatal period per woman	Continuous variable	Quantitative household survey, mmhw dashboard

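### The stated detectable difference of 0.08 ANC visits cannot be reached under the planned negative binomial model with 2300 women per group; the figure is unsupported

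*Protocol article*

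**What the plan says.** Table 1 of the Protocol article lists ANC visits as a primary outcome, defined as "ANC visits at a health facility per woman" and typed as a count variable. Under Analysis of the randomized controlled trial, the model is fixed by outcome type: "for our count outcomes, we will use negative binomial regression".

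The Power calculation section assumes "an average count of two ANC visits during pregnancy without the intervention" and says the detectable differences were obtained "using methods for cluster randomized trials". It adds: "We assumed a 20% loss to follow-up and an intra-cluster correlation of 0.05". It then names the standard method for binary outcomes, "with a 95% two-sided confidence level", and claims "an 80% power to detect an increase of 0.08 average ANC visits per woman" "if we enrolled 2300 participants per group". No standard deviation, variance or dispersion parameter for ANC visits is given.

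Two other statements bear on the point. The abstract gives 61 facilities, 29 intervention and 32 control. Study setting reports that 65% of pregnant women in the region complete at least four ANC visits.

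**The concern.** A detectable difference for a mean depends directly on the variance of the outcome. Here the variance is unstated, but the named model puts a floor under it: the negative binomial variance is mu + alpha*mu^2 with alpha at least 0, so it cannot be smaller than the mean. With a mean of two the floor is 2, which is the most favourable case for power. If 0.08 cannot be reached even there, the power section and the analysis section contradict each other on a primary outcome.

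What is at stake is how the trial is read. Someone who trusts the 0.08 figure would take a null ANC result as ruling out all but trivial effects, when the design may be able to detect only differences about three times as large.

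**Working it through.** **Inputs.** Control mean 2, difference 0.08, power 80%, two-sided 5%, 2300 per group, ICC 0.05 and loss 20% (Power calculation); 61 clusters (abstract, Study design). Average cluster size is 4600/61 = 75.4. The multiplier is 1.960 + 0.842 = 2.80.

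**Formula.** Detectable difference = 2.80 × sqrt(2 × variance × DE / n), with DE = 1 + (m − 1) × ICC.

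**Design effect.** 1 + (75.4 − 1) × 0.05 = 4.72. If 20% are lost, n = 1840 per group, m = 3680/61 = 60.3 and DE = 3.97.

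**Attempt to reproduce 0.08 at the smallest variance the model allows (2).**

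| Women per group | Clustering | Detectable difference |
|---|---|---|
| 2300 | ignored | 2.80 × sqrt(4/2300) = 0.117 |
| 2300 | ICC 0.05 | 0.117 × sqrt(4.72) = 0.254 |
| 1840 | ignored | 0.131 |
| 1840 | ICC 0.05 | 0.260 |

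The printed 0.08 is not reproduced in any row. Any alpha above 0 makes each row larger.

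**Power for 0.08 at variance 2, n = 2300.** Without clustering the standard error is sqrt(4/2300) = 0.0417, so 0.08/0.0417 = 1.918 and power is Φ(1.918 − 1.960) = 48%. With DE 4.72 the standard error is 0.0906, so 0.08/0.0906 = 0.883 and power is Φ(0.883 − 1.960) = 14%.

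**Variance that would give 0.08.** SD = 0.08 / (2.80 × sqrt(2/2300)) = 0.97, variance 0.94, or 0.47 of the mean. With DE 4.72, SD = 0.97/sqrt(4.72) = 0.45, variance 0.20, or a tenth of the mean. A variance of 0.20 around a mean of two would arise if, for example, 80% of women made exactly two visits, 10% made one and 10% made three.

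**Sensitivity.** If 0.08 is rounded from anywhere between 0.075 and 0.085, the variance-to-mean ratio without clustering is 0.41 to 0.53. A one-sided test, which the article does not use, gives 0.60. All remain below 1.

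**Could more women rescue it?** With 61 clusters, DE/n tends to ICC divided by the clusters per group (30.5) as clusters grow. The limit is 2.80 × sqrt(2 × 2 × 0.05/30.5) = 0.227 visits. At variance 2 and ICC 0.05, no number of women in these 61 clusters reaches 0.08.

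**Cross-check on another primary outcome.** Four points on a 67% facility-delivery rate needs 2098 per group without clustering, and 2300 gives 83% power. With DE 4.72, power is 27% and the detectable difference about 8.1 points. That figure too fits only if clustering is left out.

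**The mean.** If 65% of women make at least four visits, the mean is at least 0.65 × 4 = 2.6. At a mean of 2.6 the variance floor is 2.6, and the detectable difference is 2.80 × sqrt(5.2/2300) = 0.133 without clustering, or 0.289 with DE 4.72.

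**The case against.** The strongest reply is that the article states no dispersion, so the variance below the mean is back-solved from a power figure that is itself doubtful. That is correct, and it limits the point. A reader might infer that ANC counts are under-dispersed, that negative binomial regression is therefore the wrong model, and that its standard errors will be too wide. The document does not support this, for four reasons.

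- Its other figures can point the other way. Combined with a mean of two, the national figure of about half completing four visits would force every woman to zero or four visits, with variance 4. At its minimum mean of 2.6, the regional 65% gives variance 0.65 × 16 − 2.6² = 3.64. Both are over-dispersed. At higher means under-dispersion is possible, so the direction is open.
- 0.08 could have arisen without under-dispersion. Variance 2, no clustering and 5000 per group give 2.80 × sqrt(4/5000) = 0.079, and the article mentions about 10,000 women. That is not the stated enrolment, but it shows that an input error would suffice.
- Standard errors that are too wide appear only for model-based errors without clustering: 0.0209 against a robust 0.0147 in simulated counts with mean 2 and variance 1. In simulated null trials with 61 clusters of 75, a variance-to-mean ratio of 0.52 and ICC about 0.05, the model-based standard error was 0.021 against a true spread of 0.035. That is too small, with 23% rejection at a nominal 5%. The article names no variance estimator and may leave that to the analysis plan.
- With under-dispersed counts the negative binomial falls to its Poisson limit and still estimates the rate ratio consistently. For a regression on assignment alone, the Poisson and negative binomial rate ratios coincide.

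It may also be said that stratified, pairwise randomisation lowers the effective ICC. It may, but the article states 0.05, and 0.08 fails even with no clustering at all.

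**Conclusion.** The contradiction between the Power calculation and the planned count model stands, and nothing else in the article resolves it. At the stated mean, sample size, power and significance level, the best case under a negative binomial is 0.117 visits without clustering and about 0.25 with ICC 0.05, which is roughly 1.5 and 3 times the printed 0.08. Power for 0.08 is about 48% and 14%.

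The finding concerns the power figure and not the choice of model. It rests on a normal approximation for a difference in means, near-equal cluster sizes and nearly equal arms. Unequal cluster sizes would normally make the clustered figures worse.

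**What to change.** In the Power calculation:

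1. State the SD or dispersion assumed for ANC visits and its source.
2. Recompute the detectable difference with the design effect for ICC 0.05 and 61 clusters, saying whether 2300 is before or after the 20% loss, and replace 0.08 with the result. With variance equal to the mean of two it would read about 0.25 visits (0.26 after loss).
3. Reconcile the assumed mean of two with the 65% completing at least four visits under Study setting, or explain why the study population should differ.

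The negative binomial sentence can stay. Log-link Poisson regression with cluster-robust standard errors is an optional alternative. It gives the same rate ratio for a regression on assignment alone and parallels the modified Poisson model already chosen for binary outcomes.

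The cost is one recalculation and a few sentences. The design and data collection do not change. The price is a less favourable but defensible statement of what the trial can detect on this outcome.
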